## Abstract

**Background:**

Throughout the world there is an insufficient supply of donor organs to meet the demand for organ transplantations. This paper presents a protocol for a randomised controlled trial, testing whether a simple, theory-based anticipated regret manipulation leads to a significant increase in posthumous organ donor registrations.

**Methods:**

We will use a between-groups, prospective randomised controlled design. A random sample of 14,520 members of the adult Scottish general public will be contacted via post. These participants will be randomly allocated into 1 of the 4 conditions. The no questionnaire control (NQC) group will simply receive a letter and donor registration form. The questionnaire control (QC) arm will receive a questionnaire measuring their emotions and non-cognitive affective attitudes towards organ donation. The theory of planned behavior (TPB) group will complete the emotions and affective attitudes questionnaire plus additional items assessing their cognitive attitudes towards organ donation, perceived control over registration and how they think significant others view this action. Finally, the anticipated regret (AR) group will complete the same indices as the TPB group, plus two additional anticipated regret items. These items will assess the extent to which the participant anticipates regret for not registering as an organ donor in the near future. The outcome variable will be NHS Blood and Transplant verified registrations as an organ donor within 6 months of receiving our postal intervention.

**Discussion:**

This study will assess whether simply asking people to reflect on the extent to which they may anticipate regret for not registering as an organ donor increases organ donor registration 6 months later. If successful, this simple and easy to administer theory-based intervention has the potential to save lives and money for the NHS by reducing the number of people receiving treatments such as dialysis. This intervention may also be incorporated into future organ donor campaigns.

**Trial registration number:**

ISRCTN: ISRCTN92204897

## Background

There is an insufficient supply of donor organs to meet the demand for organ transplantations worldwide. Over 10,000 UK residents are currently on the waiting list for a solid organ transplant, and 3 patients die per day before they receive a transplant [1]. A recent survey found that 90% of the UK general public approve of organ donation [2]. Despite this, only 30% of people in the UK (38% in Scotland) have registered as posthumous organ donors. This discrepancy suggests that there are important barriers that deter people from registering as an organ donor. The UK Government has set aspirational targets for increasing numbers on the Organ Donor Register from the current level of 17 million to 25 million by 2013, and to increase the number of organs donated by 73% [2]. There is therefore an urgent need to identify factors that promote and overcome the barriers that deter people from registering as an organ donor [3].

Traditional social-cognitive models postulate that actions are determined by rational-cognitive factors. For example, the theory of planned behaviour (TPB) [4] suggests that actions are determined by rational cognitive attitudes, subjective norms and perceived control. According to this theoretical model, people are likely to register as posthumous organ donors when they have a positive attitude towards donation ('organ donation is a benefit to humanity'), think that significant others support registration ('my family and friends think that I should register as an organ donor'), and believe that they have the ability to register ('it is easy for me to register as an organ donor'). Indeed, most behaviour change interventions adopt such social cognitive approaches. Information is given that is designed to change people's thoughts and perceptions of a specific health behaviour. For example, in 2009 the Gift of Life campaign used the slogan "Be a hero, put the kettle on", which aimed to increase organ donation by emphasising that registration was quick and easy, thus trying to alter people's perceived control over this action. Moreover, this slogan also associated organ donation with positive perceptions ('being a hero'), thereby increasing people's positive attitude towards this action. According to the TPB, such campaigns are likely to be effective. However, without rigorous scientific evaluation, it is difficult to determine their effectiveness.

Although the TPB has been found to predict a variety of actions [5,6], including organ donation [7,8], it has been criticised for not accounting for the affective/emotional factors that guide decision making [9]. Indeed, recent research in the US [10] and the UK [11,12] has found that TPB variables are weaker predictors of organ donor registration in comparison to people's emotions and non-cognitive affective attitudes towards registration, suggesting that the key to increasing organ donor registration is to target these emotions and affective attitudes, rather than traditional social-cognitive factors. These emotions and affective attitudes can include feeling disgust towards the idea of organ donation (the "ick factor"), the superstitious belief that registration will in some way lead to harm or death for the registrant (the "jinx factor"), the desire to keep the body whole after death (bodily integrity), the fear that doctors may hasten the death of seriously ill patients in order to harvest their organs (medical mistrust), and the positive consequences of organ donation (perceived benefits). Non-donors are more likely than donors to feel these emotions and hold these negative affective attitudes, and are less likely to endorse the perceived benefits associated with organ donation [10,12]. It should be noted, however, that due to the cross-sectional design of the latter studies a causal relationship cannot be established between the affective attitudes and organ donor registration. In the present study we will address this issue by using a prospective RCT design. We also aim to extend this line of work by investigating other emotions that may affect the decision to register as an organ donor or not. Our specific focus is on the emotion of regret.

### Regret

Regret is an aversive counterfactual emotion that is experienced when people believe that their current situation could have been better if they had acted differently [13,14]. It is also possible to *anticipate *the amount of regret that one would feel for undertaking or failing to perform an action, thereby giving people a pre-emptive strategy for avoiding this aversive emotion [15,16]. The desire to avoid this emotion motivates people to undertake (or avoid) actions when they anticipate feeling regret for inaction (or action). Anticipated regret, therefore, binds people to an action by signaling the aversive emotional consequences of inaction. Indeed, research from a variety of disciplines, ranging from psychology to economics, has found that anticipated regret influences decision making and the likelihood of an action being undertaken [15-21]. Anticipated regret has also been found to predict people's intentions to perform an action and actual behavior over and above the traditional TPB components [22,23]. For example, this has been found for driving behavior [20,24,25], condom use [26-30], exercising [31,32], and weight loss [33].

A growing body of research has assessed the effectiveness of using anticipated regret in behavior change interventions. Richard and colleagues [34] found that asking students to rate how they would feel after undertaking unsafe sex increased self-reported condom use 5 months later. Although this finding is promising, it could be criticised for focusing on self-reported measures. A stronger test of the effectiveness of anticipated regret in behavior change interventions was conducted by Sandberg and Conner [18]. They invited three groups of women for cervical screening: a control group, a group sent a TPB questionnaire and a group who were sent a TPB questionnaire plus anticipated regret questions. For those that completed and returned the questionnaire attendance rates were 21%, 44% and 65% respectively. This is a quite remarkable "mere measurement" effect, given the simplicity of the intervention. Simply asking people to think about and rate the amount of regret that they anticipated for not attending a cervical screening dramatically increased screening attendance.

Similar results have been found for research with more direct relevance to organ donation. Godin and colleagues [35] randomly assigned 4,672 participants to an experimental condition that received a postal questionnaire measuring cognitions about blood donation (including anticipated regret items) or a control group that did not receive a questionnaire. Compared to control participants, the mean frequency of number of registrations at blood drives among participants in the experimental group was 8.6% greater at 6 months, and was 6.4% greater at 12 months. Significant effects were also observed for successful blood donations at 6 months and 12 months. Recently, Godin and colleagues [36] conducted a further randomised controlled trial which attempted to increase blood donation in 4,391 novice donors. They found that; (a) questionnaire completion led to a significant increase in donations, and (b) simple "if-then" planning, specifying how, where and when donation would occur (implementation intentions) led to a 12% increase in donations. Manipulating anticipated regret in this study did not augment the intervention effect. However, this study (unlike others) measured anticipated regret with isolated questions, and the authors speculated that this may have been too blatant and that participants may have interpreted the obvious anticipated regret questions as an unsubtle emotional appeal. Godin and colleagues [36] also suggest that the level of anticipated regret may need to be substantial for it to change intentions and behaviour, and failing to donate blood may not engender sufficient feelings of regret. Godin and colleagues [36] conclude "Further research is needed concerning the blatancy of the induction of anticipated regret and the role of underlying levels of anticipated regret in explaining the behavioural impact of this type of intervention" (p. 643).

The research cited above suggests that subtle anticipated regret interventions increase the likelihood of an action being undertaken. Subtly increasing the prominence of anticipated regret in the decision making process emphasises the aversive emotional consequences of inaction. The desire to avoid the aversive feeling of regret motivates people to undertake the behaviour. Essentially, anticipated regret strengthens behavioural intentions and binds the person to action, because failing to act is associated with aversive emotions. However, this is only likely to occur when the anticipated regret intervention is subtle. Blatant anticipated regret interventions are likely to be interpreted as emotional appeals, decreasing the effectiveness of the intervention. Taken together, these studies therefore suggest that people are more likely to undertake an action when they anticipate regret for inaction, and that simply asking people whether they would later regret inaction can significantly increase the likelihood of an action occurring.

### Pilot studies

The aim of the present study is to determine whether simply asking people whether they would later regret not registering as an organ donor increases verified registration. In preparation, we have conducted 3 pilot studies [for full details, see 11,12]. We found that simply asking people whether they would later regret not registering as an organ donor increased their intentions to register [12, Study 2]. Moreover, we replicated this finding with a more representative sample of the adult Scottish general public [12, Study 3]. Although these findings are promising, people do not always act upon their intentions, the well recognised intention-behaviour gap. In a third pilot study we found that asking people whether they would later regret not registering as an organ donor increased self-reported organ donor registration [11]. This latter finding suggests that anticipated regret promotes organ donor registration. However, this research can be criticised for using self-reported measures of registration. The acid test is clearly whether this intervention leads to a significant increase in *verified *registrations on the UK NHS Blood and Transplant (NHSBT) posthumous Organ Donor Register. The aim of the present study is to test whether a large scale, simple anticipated regret intervention leads to a significant increase in NHSBT verified organ donor registrations.

### Research questions

(a) Does a brief, theory-based anticipated regret intervention lead to a significant increase in organ donor registrations?

(b) If we do observe an anticipated regret effect, what is the mechanism, e.g. is it fully mediated via intentions and/or non-cognitive affective attitudes?

(c) What effect size is observed, to inform the power calculation for the next stage, a UK-wide translational study?

(d) What is the feasibility, response rate etc. to inform such a study?

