Based on our pilot data [11], we estimate that in order to identify a significant effect at the conventional .05 alpha level, at a power of .80, we would need 565 completed questionnaires per condition. As with any questionnaire based study there are likely to be many people who do not complete our survey. The response rate for this type of survey ranges from 23% to 37% [37]. Based on the conservative lower estimate (23%), we calculate that we would need to distribute 2,460 questionnaires per condition in order to gain a sufficient number of completed surveys. Furthermore, we also need to oversample to account for the proportion of the adult Scottish general public that are already registered donors. Adjusting for this, we need to distribute 3,630 surveys per condition in order to gain a sufficient number of completed surveys. Because there are four conditions in this study (for details, see below), we need to distribute a total of 14,520 questionnaires. The logistics of this national field based study will be conducted by Perspektiv, a market research company (http://perspektivred.co.uk). It should be noted that in the present study we improve on O'Carroll et al. [11] by including a no questionnaire control arm. We do not have pilot data that would allow us to conduct power calculations for this condition. However, based on the questionnaire control arm in O'Carroll and colleagues [11], we estimate that the above sample size estimates should be more than sufficient.

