### Analyses

Our primary analysis will be a logistic regression predicting donor status (registered vs. not registered) to explore the proportion of respondents who have registered as organ donors 6 months later as a function of the 4 arms. In this analysis we will control for any potential between-arm differences in age, gender and socio-economic status, if these are related to the outcome. We will conduct this regression with all participants who have not opted out of the study, regardless of whether or not they returned the questionnaire. Participants may not comply with their random assignment. That is, in this case, for some reason not complete and return the questionnaire. We will use instrumental variables (IV) regression techniques to estimate the causal effect of the intervention in compliers [see [38,39]]. Here randomization acts as the instrumental variable, compliance status as the endogenous variable. This technique is a viable alternative to traditional intention to treat (ITT) analysis. ITT treats randomization as a treatment, when in actuality it is the intervention, not the randomization that is the source of any effect. By treating assignment as an instrumental variable and intervention compliance as an endogenous variable, IV regression techniques reduce the bias in standard ITT analyses, and provide as estimate of the causal effect of the intervention in compliers [38]. These analyses will be conducted in M*Plus*-6 [40] and Stata [41]. We will also record the time interval between the questionnaire being sent out and date of organ donor registration to test for temporal effects.

If our intervention is successful, we will test the processes through which it occurs. We will assess whether the anticipated regret intervention promotes organ donor registration by increasing people's intentions to register and decreasing their emotions and non-cognitive affective attitudes towards organ donation. Essentially, we will test whether intentions and emotions mediate the effect of our intervention on registration. Simple tests of mediation will be implemented in ZUMASTAT [42]. More detailed tests of multiple and joint mediation as well as moderated mediation will be conducted using M*Plus*.

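### The plan wrongly calls ITT biased, judges effectiveness by the complier effect, and does not say which effect will size the UK-wide study

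*Protocol article*

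**What the plan says.** Four sections of the protocol article bear on this.

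- **Research questions.** Item (c) asks "What effect size is observed, to inform the power calculation for the next stage, a UK-wide translational study". It does not say whether this is the effect of being sent the pack or the effect in those who comply. Item (d) asks "What is the feasibility, response rate etc. to inform such a study".
- **Analyses.** The primary analysis is a logistic regression of registration on arm in all participants who have not opted out, whether or not they returned the questionnaire. The section then adds IV regression, with randomisation as the instrument and completion and return as compliance. Of this it says "This technique is a viable alternative to traditional intention to treat (ITT) analysis", and it argues that "ITT treats randomization as a treatment, when in actuality it is the intervention, not the randomization that is the source of any effect". It goes on to state that IV reduces the bias in a standard ITT analysis.
- **Evaluation.** Effectiveness is to be assessed by the IV logistic regression. The conclusion is nevertheless worded as a higher proportion registered in the anticipated regret arm than in the other three arms.
- **Recruitment.** The present trial was sized "in order to identify a significant effect at the conventional .05 alpha level, at a power of .80". The result was that "we would need 565 completed questionnaires per condition", and at a 23% response "we would need to distribute 2,460 questionnaires per condition in order to gain a sufficient number of completed surveys". The cited response range is 23% to 37%.

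**The concern.** The randomised all-mailed comparison is not a poor estimate of something else. It directly estimates what sending the regret pack does, and non-return is part of that effect. The complier effect answers another question: what the intervention does in those who would complete and return it. Moving from one to the other changes the estimand and corrects no bias.

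The article therefore ranks the two effects inconsistently. One section makes the all-mailed regression primary, the same section then describes that type of analysis as biased, and the next section gives the verdict on effectiveness to the IV analysis. Because (c) names no effect, a reader could take the IV estimate as the trial's effect size and carry it into the next power calculation. When most people do not return the questionnaire, the two effects differ several-fold. The choice affects both the headline result and the planning of any study that randomises people to be mailed.

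**Working it through.** **Inputs.** From Recruitment: response rate r = 0.23 to 0.37, alpha 0.05 (taken as two-sided), power 0.80, 565 completers per arm. The article gives no registration rates, so control rates p0 of 5%, 10%, 20% and 30% are assumed to show a range.

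**The plan's own figure.** 565 / 0.23 = 2,457, which agrees with the stated 2,460. The plan's one worked use of a response rate therefore divides the required number by r. It does not reduce the effect by r.

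**Ratio of the two effects.** Assume one-sided non-compliance and no effect except through return. On the risk-difference scale:

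complier effect = mailing effect / r

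- r = 0.37: 1 / 0.37 = 2.70
- r = 0.23: 1 / 0.23 = 4.35

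The plan fits logistic models. On the log-odds scale, with the assumed control rates, the ratio is about 2.3–2.6 (r = 0.37) and 3.5–4.2 (r = 0.23).

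**If the complier effect sized a mailed study.** Take the complier difference d that needs exactly 565 per arm, mail 565 / r non-donors per arm, and analyse all of them by ITT. The difference is then r × d. The sample size formula, with p̄ the mean of p0 and p1, is

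n = [1.96 √(2p̄(1 − p̄)) + 0.8416 √(p0(1 − p0) + p1(1 − p1))]² / (p1 − p0)²

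Example with p0 = 5% and r = 0.23: d = 4.29 points (5% against 9.29%). The mailing effect is 0.23 × 4.29 = 0.99 points. Power with 2,457 mailed is 0.33. For power of 0.80, 8,375 would be needed, and 8,375 / 2,457 = 3.41.

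| p0 | d (points) | r | Mailed per arm (565/r) | Power by ITT | Needed for 0.80 | Ratio |
|---|---|---|---|---|---|---|
| 5% | 4.29 | 0.23 | 2,457 | 0.33 | 8,375 | 3.41 |
| 10% | 5.56 | 0.23 | 2,457 | 0.31 | 9,128 | 3.72 |
| 20% | 7.06 | 0.23 | 2,457 | 0.29 | 9,802 | 3.99 |
| 30% | 7.88 | 0.23 | 2,457 | 0.28 | 10,193 | 4.15 |
| 5% | 4.29 | 0.37 | 1,528 | 0.47 | 3,402 | 2.23 |
| 10% | 5.56 | 0.37 | 1,528 | 0.44 | 3,640 | 2.38 |
| 20% | 7.06 | 0.37 | 1,528 | 0.42 | 3,853 | 2.52 |
| 30% | 7.88 | 0.37 | 1,528 | 0.41 | 3,977 | 2.60 |

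The gap arises because the effect shrinks by r, so the required number grows roughly with 1/r², while the inflation supplies only 1/r. Any further inflation for existing donors multiplies both columns alike and leaves the ratio unchanged.

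**If the right quantity is used.** Starting from the all-mailed difference, or from the complier risk difference multiplied by r, gives the numbers in the sixth column directly, and there is no shortfall.

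**The case against.** The strongest reply is that nothing ties the complier effect to question (c). The stated primary analysis already gives an all-mailed effect, the article calls IV an alternative and not a replacement, and the Evaluation section words its conclusion as a comparison of arms. Item (d) also collects the response rate, which converts a complier risk difference back into a mailing effect. The next study's mode of delivery and analysis are not described, and the detail of one research question may be left to a fuller document.

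Much of this stands. A reader might infer that the UK-wide study will be badly undersized. The documents do not support that, because it requires choosing the complier effect, failing to dilute it, and analysing a mailed study by ITT, and none of these is stated. Lower powers still, about 0.10–0.21, would follow with no response inflation at all, but this team's own calculation does inflate. It would also be wrong to call the IV estimate a returner-only effect, since it is not a comparison restricted to people who returned the form.

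Two things are not answered. The statement about bias in ITT is an error in the text, not an omission. The article also gives the verdict on effectiveness to an analysis other than the one it calls primary. Item (d) helps only if the response rate multiplies the effect, and the article's one worked example uses it to divide the sample size.

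**Conclusion.** The point holds as a misstatement and an inconsistency that should be corrected. The all-mailed contrast estimates the effect of mailing without bias from non-return. The complier effect is a legitimate but different quantity, and the plan should not present it as the less biased version of the same one. The multiples of 2.7 to 4.35 rest on the cited response rates holding among non-donors, on one-sided non-compliance and on the questionnaire acting only through return. They are exact only for risk differences. The loss of power, to roughly 0.3 at 23% return and 0.4 to 0.5 at 37%, is what would follow from one particular use of the complier effect under assumed control rates. It is not a predicted outcome for the next study.

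**What to change.** - **Research questions (c) and Evaluation:** state that effectiveness, and the effect size passed to the UK-wide power calculation, are the all-mailed absolute difference in new verified registrations, with 95% CI, among people not previously registered.
- **Analyses:** delete the claim that IV reduces bias in ITT. Describe the complier estimate as a supplementary answer to a different question.
- If a complier risk difference is ever used for planning a mailed study, require that it first be multiplied by the response rate.

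No new data are needed, because the Outcomes section already has the register searched for returners and non-returners alike. The cost is that the headline and planning effect becomes smaller, and the number needed for a follow-on study correspondingly larger.
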